Company 2 employs approximately 20 inspectors who work on trains serving regional routes. The company is motivated to participate in the study to obtain evidence on the preventive effect of cameras on workplace victimization, which could inform their decision regarding the potential implementation of cameras. Company 2 took part in the pilot study with a subgroup of inspectors, meaning that inspectors have either worn a camera themselves or know colleagues who have. Since the pilot study, the workforce has been reduced by half following a change in the company’s ownership. Inspectors always work alone.

Company 3 operates buses and trains in multiple regions, as well as trams in Aarhus, the second-largest city in Denmark. The company comprises two subcompanies. One is a security company contracted to conduct inspections on buses and trams; from this subcompany, 18 guards are employed to carry out inspections for Company 3. Employees always work in units of two to three. The other subcompany is a traffic company with four inspectors responsible for local train routes in a region. These inspectors always work alone. Neither subcompany uses body-worn cameras during inspections.

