#### Team-level.

Inspectors from Company 1 occasionally and Company 3 always work in pairs, potentially causing spillover effects from the expected benefits of wearing a camera to colleagues. This is accounted for in the survey by asking whether the inspector worked alone or together with a colleague during the shift. For inspectors from the subcompany hired by Company 3 who always work with two or three colleagues, the randomization and treatment are allocated at the dyad-team-level to prevent spillover effects.

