#### Moderators.

We include a variety of moderators to explore heterogeneities in the camera’s effect on victimization. One group of moderators is measured in the initial baseline survey and includes the inspector’s gender, age, ethnicity, household status, work experience in the company, BMI, prior victimization, prior sick leave due to victimization, baseline sense of safety, and attitudes toward cameras and management. Another group of moderators includes company, shift start and end time, whether the inspector worked alone or in units for some or most of the shift, camera placement on the uniform, and whether a colleague was wearing a camera. All of these moderators are pre-treatment variables and are voluntarily provided by participants.

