### Data analyses

Our data analysis plan proceeds in three stages to comprehensively evaluate the impact of body-worn cameras. We will estimate the causal effect for two primary continuous outcomes: victimization and perceived safety. First, we will estimate the Intention-to-Treat (ITT) effect, which is the effect of the random *assignment* to carry a camera, regardless of actual use. This analysis preserves the benefits of the initial randomization. We will use an Ordinary Least Squares (OLS) regression model for this purpose:

$$Y_{i}=\beta_{\text{0}}+\;\beta_{\text{1}}Z_{i}+\epsilon_{i}$$

Here, Y_i is the outcome for inspector i, and Zi is a treatment indicator equal to 1 if the inspector was assigned to the camera group and 0 otherwise. The coefficient of interest, β1, represents the ITT effect.

Second, to account for potential non-compliance (i.e., inspectors not using their assigned cameras), we will estimate the Average Treatment Effect on the Treated (ATT). This represents the effect of actually using a camera for those who complied with the assignment. We will use the random assignment as an instrumental variable (IV) for reported camera use. The effect will be estimated using a Two-Stage Least Squares (2SLS) regression.

First Stage: Predict actual camera use based on the random assignment. Here, Di is an indicator for whether inspector i reported using the camera.

$$D_{i}=\gamma_{\text{0}}+\;\gamma_{\text{1}}Z_{i}+\nu_{i}$$

Second Stage: Use the predicted camera use from the first stage (D^i) to estimate the effect on the outcome. The coefficient δATT provides our estimate of the ATT.

$$Y_{i}=\lambda_{\text{0}}+\;\lambda_{\text{ATT}}{\hat{D}}_{i}+\eta_{i}$$

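### For the team-randomized Company 3 guards, 2SLS on each guard's own reported camera may overstate the treatment-on-the-treated effect when teammates differ in camera use

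*Protocol article*

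**What the plan says.** Of the contracted guards in Company 3, the Intervention setting section says: "Employees always work in units of two to three". The Team-level section describes working with a colleague as "potentially causing spillover effects from the expected benefits of wearing a camera to colleagues". For these guards, it says, "the randomization and treatment are allocated at the dyad-team-level to prevent spillover effects".

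The Data analyses section then sets out the 2SLS: "We will use the random assignment as an instrumental variable (IV) for reported camera use". Treatment received is individual: "Di is an indicator for whether inspector i reported using the camera". Of the resulting coefficient it says: "This represents the effect of actually using a camera for those who complied with the assignment". Non-compliance is described there as failing to use an assigned camera.

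The Moderators section lists "whether a colleague was wearing a camera" among the moderators. That item does not enter the 2SLS equations.

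**The concern.** For the guards, the instrument is shared by the team while treatment received is individual. The protocol's reason for sharing the instrument is that a teammate's camera may act on a colleague. Take a camera-assigned shift on which guard A wears a camera and guard B does not. B is recorded as untreated, although the passengers B meets also face A's camera. If A's camera changes B's experience, assignment affects B's outcome by a path that does not run through B's own camera. That is a failure of the exclusion restriction. The ITT numerator includes the effect on B, while the first-stage denominator does not count B as exposed, so the ratio is too large in absolute value.

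At stake is the size of the treatment-on-the-treated estimate, which the Introduction presents as an advantage of the survey design. Over the compliance range examined below, poorer compliance among guards would make the camera look stronger.

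**Working it through.** The protocol states no compliance rate, spillover size or 2SLS result, so there is no figure to reproduce.

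**Inputs from the protocol.** 18 team-allocated guards in units of two to three, about 20 inspectors in Company 2 and four in Company 3's other subcompany (Intervention setting); up to 60 inspectors in total (Sample size and power analysis); own-use D (Data analyses).

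**Assumed.** Compliance p on camera shifts, independent between teammates; a fraction s of the effect reaching a non-wearer whose teammate wears a camera; team size k; and, at first, camera-free control shifts.

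**Step 1. Estimator.** With one binary instrument, 2SLS equals ITT / (E[D|Z=1] - E[D|Z=0]).

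**Step 2. Guards.** Let tau be the effect on a wearer.
- ITT = tau x {p + s(1-p)[1-(1-p)^(k-1)]}, and the first stage = p.
- Factor = 1 + s(1-p)[1-(1-p)^(k-1)]/p. For pairs this is 1 + s(1-p), which is 2 - p at s = 1.
- Pairs, s = 1: 2 - 0.9 = 1.10 and 2 - 0.8 = 1.20.
- Pairs, s = 0.5: 1 + 0.5 x 0.1 = 1.05 and 1 + 0.5 x 0.2 = 1.10.
- Triples, s = 1, p = 0.8: 1 + 0.2 x 0.96/0.8 = 1.24.
- s = 0, or p = 1: 1.00.
- Teammates complying or failing together, with one camera carrying the full effect: 1.00, because no team is split.

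A simulation of 1,000,000 pairs (true effect -0.20, p = 0.8, s = 1) gave -0.239 with own-use D and -0.199 with D defined as any camera worn in the team, that is, factors of 1.20 and 1.00.

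**Step 3. Cameras worn on control shifts.** For pairs with s = 1, and wear rates c1 and c0 on camera and control shifts, the factor is {[1-(1-c1)^2] - [1-(1-c0)^2]}/(c1-c0) = 2 - (c1+c0). This gives 1.10 at 0.8/0.1, 1.00 at 0.9/0.1 and 0.90 at 0.9/0.2.

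**Step 4. Pooled analysis.** If all 18 guards enrol among 60 inspectors (w = 0.30) and everyone else works alone, the factor for pairs at s = 1 is 1 + w(1-p): 1.03 at p = 0.9, 1.06 at p = 0.8 and 1.09 at p = 0.7. Company 1 inspectors, however, sometimes work in pairs and are randomized individually, so a control inspector may stand beside a wearer. If a share q of all shifts is of this kind, and the colleague wears a camera with probability r, the factor becomes 1 + w(1-p) - qr. Taking q = 0.05 to 0.30, r = 0.25 or p/2, and p = 0.7 to 0.9 (all assumed):
- highest: 1 + 0.09 - 0.05 x 0.25 = 1.08;
- lowest: 1 + 0.03 - 0.30 x 0.45 = 0.90 (rounded).

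**Step 5. Excluding Company 1.** If everyone enrols, w = 18/(20+18+4) = 18/42 = 0.43, and the factor at s = 1 is 1.04 at p = 0.9 and 1.09 at p = 0.8. The Company 1 offset is absent here.

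**Step 6. The alternative coding.** For pairs at p = 0.8, any-camera D has a first stage of 1 - 0.2^2 = 0.96. Relative to the wearer's own effect:

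| Spillover s | ITT/tau | Own-use D (divide by 0.80) | Any-camera D (divide by 0.96) |
|---|---|---|---|
| 1 | 0.96 | 1.20 | 1.00 |
| 0.5 | 0.88 | 1.10 | 0.92 |
| 0 | 0.80 | 1.00 | 0.83 |

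Neither coding is right for every s.

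**The case against.** The strongest case on the other side has four parts.

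- **The bias is conditional.** A reader might infer that the estimate is certainly overstated, that the error always points away from zero, or that it vanishes only if a camera affects nobody but its wearer. The documents support none of these. Spillover is described only as a possibility, and nothing says that teams split on camera use. Full compliance, or compliance as a unit with one camera sufficient, also removes the bias, and enough control-shift wear cancels or reverses it. Such wear is less likely in Company 3, which does not otherwise use cameras during inspections, but it is not excluded. This objection stands and limits the conclusion.
- **The consequence is small.** The pooled factor is near 1 and Company 1 pairs can pull the other way. Recoding D rescales the estimate and its standard error nearly together, so the test essentially follows the ITT test. This stands: the issue is magnitude, not detection.
- **The remedy has its own assumption.** Any-camera D supposes that one camera suffices, and it moves away from the camera on the inspector's own uniform, which the Instruction section calls the strongest test. This also stands, and argues for adding the coding rather than replacing the existing one.
- **An article condenses.** Special coding for one subgroup could sit in a fuller analysis plan. This stands only in part, because the article states the treatment-received variable explicitly, as own use.

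Nothing else in the article covers the point. Dyad-clustered standard errors address variance, inspector fixed effects leave D unchanged, and the colleague's camera is used only as a moderator.

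**Conclusion.** The point holds conditionally. Team allocation and own-use D do not match. Where teammates differ in camera use and a teammate's camera has an effect in the same direction, the exclusion restriction fails for those shifts. With camera-free control shifts, the guards' treatment-on-the-treated estimate is then biased away from zero. A plausible size for pairs is 5% to 20% (half to full spillover, p = 0.9 to 0.8, independent compliance), but compliance and spillover are assumptions, not figures from the protocol. The pooled factor of 1.03 to 1.09 should not be read as the plan's net bias: once Company 1 pairs are allowed for, the range is about 0.90 to 1.08 and the sign is open. The ITT is unaffected. The matter is worth settling before analysis because it concerns a named estimand and is cheap to address.

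**What to change.** For team-allocated shifts, add a 2SLS in which D = 1 if any member of the unit reported wearing a camera, taken from members' own reports and checked against the item on the colleague's camera. Label it the effect of a camera in the unit. Keep own-camera D for inspectors working alone. Report this beside the own-use coding, both pooled and in the analysis excluding Company 1.

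State the assumption behind each coding: for the team-allocated guards, own-use D assumes no spillover, and any-camera D equals the wearer's own effect only if one camera suffices. Reporting both shows how far the result depends on this.

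The cost is one extra analysis on items already collected. The downside is a unit-level estimand for the guards, so the pooled version combines a unit-level exposure with an individual one and must say so.

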### Randomization

#### Camera use.

The study randomizes at the level of inspector shifts. Each inspector is assigned to wear a camera during a randomly selected 50% of their shifts over the study period (treatment) and to work without a camera during the remaining shifts (control). Four hours before each shift, participants receive an automated text message indicating whether they must wear a camera for that shift. If a shift starts before 12 pm, the text message is sent the evening before at 8 pm to avoid contacting participants between 8 pm and 8 am. The treatment message is sent within a time span that allows participants to have time to bring the camera to work while minimizing the risk that participants select routes based on whether they carry the camera or not (as some inspectors have freedom in choosing routes). While this design informs inspectors about their condition assignment in a timely manner, it does not eliminate the risk that inspectors adjust their inspection style and manner of coping with passenger conflicts in anticipation of their assigned condition. To assess this bias, we will examine whether outcomes vary across different notification times, on the assumption that shorter notice leaves less room for anticipatory adjustments.

The block-randomization design guarantees an even 50/50 split between treatment and control shifts for every participating inspector. Compared to the field trial by Ariel and colleagues [4], this approach offers key advantages: it ensures treatment and control observations are independent of inspector- or shift-specific characteristics, removes clustering by inspector, increases statistical power, and makes it more likely that randomization produces genuine *ceteris paribus* conditions [31,32]. Despite these strengths, this design carries a risk of contamination, as the same inspectors alternate between treatment and control shifts and may carry learned behaviors, fatigue effects, or other carry-over biases from one condition to the other [see, e.g., 33].

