### Survey

#### Baseline and background survey.

Before the intervention, inspectors complete a questionnaire assessing baseline self-perceived safety, attitudes toward body-worn cameras, trust in management, and sociodemographic information such as age, gender, ethnicity, and height and weight (for calculating body mass index, BMI). These data enable the examination of potential treatment effect heterogeneities—for example, whether women or individuals with lower BMIs experience greater benefits from body-worn cameras than colleagues with a more imposing physical presence. Identifying such heterogeneities will enhance the generalizability of the findings to other companies and contexts, providing more nuanced insights than a simple average treatment effect.

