Finally, to explore potential moderators, we will investigate treatment effect heterogeneity. We will use causal forests, a machine-learning method designed to estimate Conditional Average Treatment Effects (CATEs), defined as τ(X)=E[Y(1)−Y(0)|X = x]. This non-parametric approach will allow us to flexibly explore how the treatment effect varies across a range of pre-specified inspector characteristics (X) without being constrained by linear interaction terms. These explorative subgroup analyses will be conducted and disseminated with careful consideration of sensitive moderator variables such as BMI and ethnicity. Further, we acknowledge that our exploratory subgroup analyses imply an increased false-positive rate due to multiple comparisons [38], which will be addressed by interpreting statistical significance tests conservatively and clearly labeling these results as’exploratory’ in the Results section.

For all OLS and 2SLS regression models, we will calculate cluster-robust standard errors to account for the statistical dependence between inspectors working in dyads. Furthermore, as a robustness check, we will re-estimate our primary models including inspector fixed effects to control for any unobserved, time-invariant characteristics of the individuals.

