### Sample size and power analysis

The current study will sample approximately 3,000 shifts from up to 60 ticket inspectors employed by the three companies during a three to four months intervention period. As mentioned, our block-randomization design using work shifts, not individual inspectors, ensures that treatment and control observations are independent of inspector characteristics, effectively making the 3,000 shifts the sample unit [32].

Importantly, the sample size in the current study will provide very high statistical power to detect even small effects. A priori power analysis indicates that the planned sample size will yield 90% power to detect very small effect sizes (Cohen’s *f*^2^ = 0.003) in a regression model. Even under conservative assumptions of substantial attrition—such as 20% missing data due to loss of interest among inspectors who fail to complete the survey—the study is still expected to maintain 90% power to detect similarly small effects (Cohen’s *f*^2^ = 0.004).

Further data-structural and model-specification choices may reduce this power. For example, this could result from the use of cluster-robust standard errors to account for inspectors working in dyads, the imbalance in the number of observations across experimental conditions, or other anomalies that may arise during data collection. Nevertheless, given that our power calculations indicate the ability to detect even very small effects, it is unlikely that such factors will meaningfully compromise the overall capacity of the analyses to detect effects of a small magnitude.

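### For moderators fixed within an inspector, the causal forest should be split and clustered by inspector; the article's stated basis, shifts as the sample unit, can raise false positives above 5%

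*Protocol article*

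**What the plan says.** The Data analyses section proposes causal forests to "flexibly explore how the treatment effect varies across a range of pre-specified inspector characteristics". The Moderators section explains where these come from: "One group of moderators is measured in the initial baseline survey". By my count that group holds 11 variables: gender, age, ethnicity, household status, work experience, BMI, prior victimization, prior sick leave, baseline safety, and attitudes to cameras and to management. Each has one value per inspector.

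Three statements bear on the unit of analysis:

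- Camera use (under Randomization) says that block randomization of shifts "removes clustering by inspector, increases statistical power".
- Sample size and power analysis describes the design as "effectively making the 3,000 shifts the sample unit".
- Data analyses limits the cluster correction: "For all OLS and 2SLS regression models, we will calculate cluster-robust standard errors to account for the statistical dependence between inspectors working in dyads". Inspector fixed effects appear only as a robustness check on the primary models.

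The forest's unit, subsampling scheme and cluster level are not stated. For the subgroup analyses the article admits a raised false-positive rate, names multiple comparisons as the cause, and answers with conservative interpretation and an exploratory label. The Baseline and background survey section nevertheless expects these results to travel: "Identifying such heterogeneities will enhance the generalizability of the findings to other companies and contexts".

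**The concern.** Randomizing shifts within inspectors makes assignment independent of every inspector trait, and this supports the average camera effect. It does not multiply the number of people on whom a trait is observed. Whether the effect depends on BMI is answered by comparing the effects of low-BMI and high-BMI inspectors, and there are at most 60 inspectors to compare. Fifty shifts sharpen the estimate of one inspector's effect but add no further BMI value.

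The general statements that inspector clustering is gone and that shifts are the sample unit are therefore wrong for this analysis. A forest run on that basis has two problems. Its standard errors omit the ordinary variation in effect from one inspector to another. Its honest halves and held-out data also contain shifts of the same inspectors. Eleven traits on 60 people can nearly identify individuals, so the forest can learn a person's own effect and then confirm it on that person's other shifts.

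At stake is a reported pattern by sex, BMI, ethnicity or attitude, offered as transferable to other companies, that reflects only which individuals took part.

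**Working it through.** **Inputs from the article.** "approximately 3,000 shifts from up to 60 ticket inspectors employed by the three companies", so 3,000/60 = 50 shifts per inspector. Allocation "guarantees an even 50/50 split between treatment and control shifts for every participating inspector", so 25 camera and 25 control shifts each. Eleven inspector-level moderators.

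**Inputs assumed.** Nominal two-sided 5%. The between-inspector SD of the camera effect, *s*, in outcome SD units, is not in the documents; 0 to 0.4 is shown.

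**The plan's own figure.** The article states 90% power at f² = 0.003. With 3,000 independent shifts and one predictor this gives 91.2% one-sided or 85.1% two-sided, so the stated figure fits a calculation that takes each shift as an independent unit. For scale, f² = 0.003 corresponds to d = 2√0.003 = 0.11 SD.

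**False-positive rate for one trait unrelated to the effect.**

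1. With unit outcome variance within inspector, the estimated effect for one inspector has sampling variance 1/25 + 1/25 = 4/50 = 0.08.
2. Across inspectors its true variance is 0.08 + s².
3. A shift-level analysis sees the unmodelled differences only as extra residual variance of s²/4 and assumes 0.08 × (1 + s²/4).
4. The ratio is R = (0.08 + s²) / [0.08 × (1 + s²/4)]. The actual size is 2 × [1 − Φ(1.96/√R)].

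At s = 0.2: R = 0.12/0.0808 = 1.485, 1.96/√1.485 = 1.61, size 10.8%.

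| s | R | size, 50 shifts each | size, 40 shifts each (20% missing) |
|---|---|---|---|
| 0 | 1.000 | 5.0% | 5.0% |
| 0.1 | 1.122 | 6.4% | 6.1% |
| 0.2 | 1.485 | 10.8% | 9.6% |
| 0.3 | 2.078 | 17.4% | 15.1% |
| 0.4 | 2.885 | 24.9% | 21.5% |

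**Simulation check** (60 inspectors × 50 shifts, 2,000 runs, camera-by-moderator interaction, shift-level robust errors):

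| s | outcome centred by inspector (ICC 0 or 0.2) | not centred, ICC 0.2 |
|---|---|---|
| 0 | 5.0–5.8% | 3.0–3.2% |
| 0.1 | 6.8–7.3% | 4.4–4.6% |
| 0.2 | 11.6–13.1% | 7.4–9.0% |
| 0.3 | 17.2–21.2% | 14.3–15.0% |

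With the inspector as the unit, the rate is 4.4–6.1% (inspector-level regression) or 4.4–7.6% (inspector-clustered errors) over the values of s simulated.

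**Does a multiplicity correction help?** With 11 independent null moderators, multiplicity alone gives 1 − 0.95¹¹ = 43% for at least one hit. Bonferroni uses 0.05/11, critical value 2.84. Replacing 1.96 by 2.84 in step 4, the chance of at least one hit is 4.9%, 7.8%, 19.8% and 42.5% at s = 0, 0.1, 0.2 and 0.3. The correction works at s = 0 and fails as s grows.

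**Overall forest heterogeneity test** (nominal one-sided 5%, moderators unrelated to the effect). Two simplified forests, neither of them the authors' software, were simulated:

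| s | A, split by shift | B, split by shift |
|---|---|---|
| 0 | 4% | 13% |
| 0.1 | 16% | 27% |
| 0.2 | 57% | 74% |
| 0.3 | 96% | 99.5% |

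Split and clustered by inspector, A stays at 4–7% and B at 11–12.5% over the same range. B exceeds 5% even at s = 0, so only the contrast is informative: rejection rises with s when splitting by shift and stays flat when splitting by inspector.

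**The case against.** **The article never says that the forest runs on shifts.** This is correct. The sample-unit phrase stands in the power section, and silence about the forest's clustering does not mean there is none; a separate analysis plan may set it. A reader might infer from the three statements that an unclustered forest is planned, but the text does not establish that. What stands is narrower: the article's general claims about clustering and the sample unit are wrong for inspector-level moderators, and the only cluster correction it names covers neither the forest nor the inspector.

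**The inflation may be small.** This too is correct. It is absent at s = 0 and slight at 0.1, and without centring by inspector the simulated rates are lower still. With a mean effect of −0.1 SD and normally distributed effects, s = 0.2 to 0.3 would mean that cameras worsen outcomes for about 31–37% of inspectors. A reader might infer that false positives occur far more often than 5% whatever s is; the documents give no s and do not support that. On the other hand, s = 0 would mean there is no heterogeneity to explore, and the analysis is planned because there may be some.

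**The large forest percentages answer another question.** They are overall rejections in data where inspectors truly differ, not rates at which BMI or gender is wrongly named. They should not be quoted as moderator-specific error rates.

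**The analyses are exploratory and labelled so.** This limits the harm, and the conservative reading is welcome. But the label answers multiplicity, not the unit of analysis. One could also argue that inference concerns only these inspectors, but the stated aim of generalizing to other companies makes the inspector the relevant unit.

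**Conclusion.** The point holds in a conditional form. For moderators constant within an inspector, the information comes from at most 60 inspectors, and the article's stated basis for analysis does not reflect this. If the forest is run on that basis and inspectors differ in effect for reasons unrelated to a trait, the false-positive rate for that trait is about 5%, 6%, 11% and 17% at s = 0, 0.1, 0.2 and 0.3. This assumes 60 inspectors with 50 shifts each, a 25/25 split, a nominal two-sided 5% and unit outcome variance within inspector. An overall heterogeneity test split by shift also rejects increasingly often as s grows; one split by inspector does not.

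The point does not reach moderators that vary by shift, such as start time or working alone, and it does not concern the main ITT and 2SLS estimates. The text does not support saying that the trial will report false subgroup effects. The change is worth making because it is cheap and the existing caveats do not do its work.

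**What to change.** In Data analyses, state that the causal forest is subsampled, honestly split and evaluated by whole inspectors (by team for the Company 3 guards who are allocated jointly), and that any heterogeneity test or subgroup CATE uses standard errors clustered at that level. Keep the multiplicity caution in addition.

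In Camera use and in Sample size and power analysis, qualify the statements on clustering and the sample unit: for inspector-level moderators, the effective sample is the number of inspectors, up to 60.

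The cost is a few sentences and a cluster setting in the forest software, with no new data. The downside is wider intervals and visibly low power for these exploratory moderators, which is an accurate picture of what 60 inspectors can show.

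### The primary ITT and 2SLS models omit the inspector blocks used in the randomization and cluster only on dyads, so the primary standard error is generally miscalibrated, in a direction that depends on how much the effect varies between inspectors

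*Protocol article*

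**What the plan says.** - **Randomization.** The article (Randomization, Camera use) states that the block design "guarantees an even 50/50 split between treatment and control shifts for every participating inspector". The inspector is therefore the block. For the guards hired by Company 3, allocation is by team (Team-level).
- **Claim drawn from the design.** The same section says that this approach "removes clustering by inspector, increases statistical power". The sample size section then takes the 3,000 shifts as the sampling unit.
- **Primary model.** Data analyses says "We will use an Ordinary Least Squares (OLS) regression model for this purpose" and prints an equation with an intercept and the assignment indicator only. The two 2SLS equations have the same form. None has an inspector or block term.
- **Standard errors.** For every OLS and 2SLS model, "we will calculate cluster-robust standard errors to account for the statistical dependence between inspectors working in dyads". The inspector is not named as a cluster.
- **Inspector effects.** These appear only in the statement that "as a robustness check, we will re-estimate our primary models including inspector fixed effects".

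**The concern.** Blocking makes assignment orthogonal to inspector. It does not make some 50 outcomes reported by one person independent, and it does nothing about an effect that differs from person to person. The precision that blocking buys reaches the standard error only if the blocks are in the model. Clustering on dyads does not help where inspectors work alone: all of Company 2, the four train inspectors in Company 3, and the daytime work in Company 1.

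What is at stake is the confidence interval for the main result. If the effect is much the same for everyone, the interval is wider than it need be. If the effect differs enough between inspectors, the interval is too narrow for a conclusion about inspectors in general. The protocol plans for such differences (baseline survey, moderators, causal forests) and hopes to generalize to other companies and contexts.

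**Working it through.** **Inputs from the article.** N = 3,000 shifts, J = 60 inspectors, so m = 3,000/60 = 50 shifts each, split 1:1. The stated power is 90% at f² = 0.003, or at f² = 0.004 with 20% missing (2,400 shifts). Alpha and sidedness are not stated.

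**Inputs assumed.** ICC is the share of outcome variance between inspectors, tried at 0.1, 0.2 and 0.3. Tau is the SD of the inspector-specific effect in outcome SDs, tried from 0 to 0.3. The article gives neither.

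**Step 1: the plan's own figure.** With independent shifts, the noncentrality is 3,000 × 0.003 = 9.0 and 2,400 × 0.004 = 9.6.
- Two-sided 0.05: power 85.1% and 87.2%.
- One-sided 0.05: power 91.2% and 92.7%. The f² values that give exactly 90% are 0.00286 and 0.00357, which round to the stated 0.003 and 0.004.

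So the stated figures fit a one-sided 5% test of independent shifts. The steps below use two-sided 0.05, for which 90% power needs d = (1.96 + 1.2816) × sqrt(4/3,000) = 0.118.

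**Step 2: formulas** (total outcome variance 1).
- True variance of the camera minus no-camera difference, over a wider population of inspectors: 4(1 − ICC)/N + tau²/J.
- Variance reported without blocks or inspector clustering: (4 + 2·tau²)/N.
- Variance reported with inspector fixed effects but no inspector clustering: (4(1 − ICC) + tau²)/N.

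**Step 3: constant effect (tau = 0).** Reported/true SE = 1/sqrt(1 − ICC).

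| ICC | Reported/true SE | Type I error |
|---|---|---|
| 0.1 | 1.05 | 3.9% |
| 0.2 | 1.12 | 2.8% |
| 0.3 | 1.20 | 1.9% |

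At ICC 0.2 and d = 0.118, power is 92.4% without the blocks and 95.2% with them.

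**Step 4: where the direction changes.** The reported SE is too narrow when 4 + 2·tau² < 4 − 4·ICC + 50·tau², that is, when tau² > ICC/12. The thresholds are tau = 0.09, 0.13 and 0.16 at ICC 0.1, 0.2 and 0.3.

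**Step 5: varying effect, ICC 0.1, inference beyond the enrolled inspectors.**

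| tau | Reported/true SE | Type I error |
|---|---|---|
| 0.05 | 1.04 | 4.2% |
| 0.1 | 0.99 | 5.2% |
| 0.2 | 0.85 | 9.4% |
| 0.3 | 0.72 | 15.9% |

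For tau = 0.2: true variance 3.6/3,000 + 0.04/60 = 0.001867; reported 4.08/3,000 = 0.001360; sqrt(0.001360/0.001867) = 0.85.

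**Step 6: does the planned robustness check repair this?** With a constant effect, yes. With ICC 0.1 and tau 0.2, fixed effects without inspector clustering report 3.64/3,000 = 0.001213. The ratio is sqrt(0.001213/0.001867) = 0.81 and type I error is 11.4%; simulations gave 11.5% to 12.4%. That is worse than the unblocked model.

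**Step 7: dyads.** The article does not say whether a dyad is a lasting pair or a pair on one shift. A simulation with 42 solo inspectors and 9 team-randomized dyads (ICC 0.2, shared dyad-shift variance 0.2) covered both. Clustering on the pair-shift gave SE ratios of 1.11 at tau 0 and 0.75 at tau 0.3; clustering on the lasting pair gave 1.07 and 0.82. The conclusion is the same. Clustering on inspector, or on team for the dyads, kept type I error between 4.4% and 6.0% in every scenario tried.

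**The case against.** The strongest reply has four parts.

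1. *A varying effect does not by itself make the interval too narrow.* This stands. A reader might infer that any variation between inspectors does so. Step 4 shows that tau must pass a threshold that rises with the ICC. Below it the interval is still too wide, and near it the test is almost nominal (5.2% at ICC 0.1, tau 0.1).
2. *The anti-conservative cases need large assumed variation.* This stands as a caution. A tau of 0.2 to 0.3 SD is about two to three times the mean effect the trial is sized for (2 × sqrt(0.003) = 0.11 SD). An exploratory search for moderators does not show that variation is that large.
3. *The average effect among the enrolled inspectors needs no inspector clustering.* This also stands. For that target, block-adjusted shift-level errors suffice and the unblocked model is conservative. The inspectors are volunteers, and the analysis section does not name a wider population. The article's aims of informing other companies and contexts do point beyond them, so the target needs to be stated.
4. *Fixed effects are already planned.* This stands in part. They repair the constant-effect case, but they are secondary, and step 6 shows that they do not repair the varying-effect case.

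Two other inferences are not supported. Leaving out the blocks does not bias the estimate, because allocation is 50/50 in every block. Nor does ignoring inspector correlation overstate power when the effect is constant: with assignment balanced within inspector, it understates it. The definition of the indicator ("a treatment indicator equal to 1 if the inspector was assigned to the camera group and 0 otherwise") is loose wording, since shift-level randomization is clear elsewhere, and no result depends on it.

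**Conclusion.** The concern holds in a limited form. The primary ITT and 2SLS models leave out the blocks that the randomization uses, the inspector is not a cluster, and the statement that the design "removes clustering by inspector" is wrong. The primary standard error is therefore generally miscalibrated, around an unbiased estimate.

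With a constant effect the error is a modest loss of precision: an SE 5% to 20% too wide for ICC 0.1 to 0.3. Undercoverage arises only for inference beyond the enrolled inspectors and only when tau exceeds about sqrt(ICC/12). In that case neither planned analysis is calibrated. All sizes rest on assumed ICC and tau, on 60 inspectors with 50 shifts each, and on a two-sided 5% test.

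**What to change.** - Make the model with inspector block effects primary for ITT and for both 2SLS stages, using team effects for the team-randomized guards.
- Cluster standard errors on inspector, or on team for those guards, with a small-sample correction because there are only about 60 clusters. Say what a dyad is.
- Keep the unblocked OLS as a sensitivity analysis.
- State whether inference is to the enrolled inspectors or to inspectors more widely.
- Delete the claim that the design removes clustering by inspector.

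**Cost.** Only analysis wording changes; no data collection is affected. If effects really differ between inspectors, intervals widen. At ICC 0.1, with 59 degrees of freedom (critical value 2.00), power at d = 0.118 is about 88%, 77% and 61% for tau 0.1, 0.2 and 0.3, and the f² detectable with 90% power rises to 0.0037, 0.0050 and 0.0073. If the effect is constant, precision improves.
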